#### Secondary outcomes

In order to test differences in secondary endpoints, effect sizes and CIs will be calculated. Repeated measures analysis of variance and covariance will be conducted to test effects on continuous secondary outcomes related to stress/coping (i.e., knowledge, symptoms of stress, coping resources) and MHL (knowledge and attitudes about mental disorders and help-seeking). In addition, cost-effectiveness analyses and cost-utility analyses of the study intervention will be conducted. Cost-effectiveness analyses include the calculation of the incremental cost-effectiveness ratio (ICER). The ICER indicates the additional cost for each additional (primary) outcome that has to be paid under routine care conditions. During these analyses, standard health economy techniques will be applied, such as bootstrapping techniques for estimating ICER variability, the calculation of cost-effectiveness acceptability curves (CEAC), and calculation of willingness-to-pay (WTP) criteria [52, 58]. In addition, a cost-utility study will be conducted that requires the transformation of longitudinal quality of life data (assessed with the KIDSCREEN-10) into preference measures, for the calculation of quality-adjusted life years (QALYs) lost or gained during follow-up in order to calculate costs per QALY as generated by the intervention.

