### Enrollment and randomization

Permission to contact schools within the regional districts of all five recruiting study sites (Hamburg, Heidelberg, Leipzig, Marburg, Schwäbisch Gmünd) will be requested from federal authorities. A total list of schools in the regional districts will be acquired. Eligible schools will be contacted and informed, in random order, about the possibility to participate, until the prospected sample size is reached (in total *N* = 15,000 C&A). Following the baseline screening, healthy C&A (not fulfilling allocation criteria for any other ProHEAD program; see [31–34]) will be invited to participate in the *StresSOS* online program. C&A will receive an email including information about the trial and access details for the baseline assessment within the *StresSOS* trial. After completing this assessment, participants will be randomized with equal probability (in a 1:1 ratio) to the online *StresSOS* program and the online control group (online program on healthy nutrition). The allocation will be randomized, stratified for gender and school type. Randomization will be conducted externally and will follow a permutated block design with variable, randomly arranged block sizes. Following randomization, participants will be contacted informing them about their allocation to the respective intervention group and will receive access details for the specific online program.

In the face-to-face *StresSOS* program, the entire class will be invited to participate in the trial. Parallel to the online trial, eligible schools will be contacted and informed in random order about the possibility of participating in the program. Blinding is not possible. Participating C&A and experts are not unaware of the interventional procedure. However, assessments are based on self-report and take place within the school-based screening, which helps to avoid biased assessment of results.

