The *StresSOS* face-to-face program is a classroom-based intervention, administered by experts (advanced students, mental health professionals). One weekly session lasts 90 min. A variety of teaching methods will be included (e.g., presentations, group discussion, group activities, role play, video presentations, games, quizzes, answer sheets, homework). The *StresSOS* online program will be completed by C&A autonomously (e.g., from their computer at home). A weekly session takes approximately 20–90 min according to individual needs and preferences. The program contains information and psycho-educational materials, interactive online training, quizzes, and exercises on the session’s topic. An individualized monitoring and feedback module is implemented. Once a week participants will receive an email that reminds them about the upcoming session. Via a link in the email they can access an online monitoring questionnaire, which asks them whether they have completed their “homework” (“Your turn! Give it a try”) and whether they liked it. The following individualized feedback will reinforce positive behaviors and offer suggestions and recommendations in case C&A did not complete their homework or did not experience the task as helpful or good. A group chat moderated by an expert takes place once a week. C&A are invited to join the chat on a voluntary basis and have the opportunity to ask questions of the expert or discuss their experiences within the program with their peers. Finally, the program contains a news blog. Moderators frequently upload information to the news blog and provide up-to-date news about the topic.

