### Sample size calculation

In the control condition, 30% transitions from “healthy” to “at-risk” are expected. Further, it is anticipated that participation in *StresSOS* (online or face-to-face) will prevent 50% of these transitions, i.e., reduce the transitions to 15%. The sample size calculation is primarily based on the non-inferiority trial (Study B). Assuming equal efficacy for online and face-to-face delivery of *StresSOS* (i.e., 15% transition to “at-risk”), a non-inferiority margin δ = 5%, and an allocation ratio of 5:1, 2920 participants (2500 in the online and 420 in the face-to-face condition) need to be included in Study B to test non-inferiority with 80% power at α = 5% (Z-test). For Study A, the proposed sample size will allow one to assess the assumed group differences precisely (95% confidence interval (CI) +/− 2.3%); i.e., it allows one to test clinical significance of the efficacy of online *StresSOS* (between-group difference > 10%) with more than 95% power. The sample size may be larger, as all C&A who do not meet the inclusion criteria of the other four ProHEAD trials for C&A with (sub-threshold) mental health problems [31–34] are included. Even if the proposed sample size is reached, the program will still be offered to “healthy” C&A.

Based on previous experiences in school-based settings, there may be an expected loss to follow-up rate of 15% for the face-to-face sample [36] and 25% for the program-specific assessments of the online sample. Based on the literature [19] and the experiences within the consortium, the expectation is that about 33% of the participants in the online *StresSOS* condition will be compliant and work through the modules as expected, 33% will utilize about half of the modules, and 33% will log in only once.

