### Statistical analyses

#### Study A

Differences in the transition rate from the “healthy” group to the “high-risk” or the “mental health problems” group at 12 months follow-up will be tested with Fisher’s exact test (two- sided, α = 5%). The 95% CIs for the group difference will be calculated in order to test clinical significance (> 10% difference) of the online *StresSOS* efficacy. Analyses will be based on intention-to-treat (ITT) principles. Missing values will be imputed with the predictive mean matching method using the R package mice (Multivariate Imputation by Chained Equations [55]).

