#### Study B

Non-inferiority [56] of online delivery of *StresSOS* will be tested against the null hypothesis H0: Difference (% transitions face-to-face – % transitions online) < 5% (Z-test, α = 5%). Non-inferiority is assumed if the upper limit of the 95% CI of the empirical group difference is less than 5% (CI inclusion approach). Propensity score weighting methods will be applied to control for potential confounders between the online and the face-to-face condition [57]. The covariates taken into account for the propensity score procedure will be, for example, psychological strain, coping skills, age, gender, and type of school. Tests will be based on ITT principles; missing values will be imputed.

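### The Study B secondary analyses name repeated-measures ANOVA/ANCOVA with no class term, although the face-to-face arm is enrolled and taught as whole classes, so online versus face-to-face intervals would be too narrow

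*Protocol article*

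**What the plan says.** The protocol article fixes the method for the continuous secondary outcomes under Statistical analyses, Secondary outcomes: "Repeated measures analysis of variance and covariance will be conducted to test effects on continuous secondary outcomes". That section does not say whether it covers Study A, Study B or both, and it mentions neither class nor school.

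Two other places show how the face-to-face arm is formed. Under Enrollment and randomization, "the entire class will be invited to participate in the trial". Under StresSOS (online or face-to-face), the "face-to-face program is a classroom-based intervention, administered by experts", with weekly 90-minute sessions. Online pupils work through the modules on their own and are randomised individually 1:1 against the control programme.

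On missing data and confounding, the Study A section says: "Missing values will be imputed with the predictive mean matching method using the R package mice". The Study B section says: "Tests will be based on ITT principles; missing values will be imputed". It also says: "Propensity score weighting methods will be applied to control for potential confounders between the online and the face-to-face condition". The Secondary outcomes section neither repeats nor withdraws these provisions.

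**The concern.** Pupils in one class share a school, a session leader, group activities and discussion. Their scores on knowledge, coping and attitudes after the programme will tend to resemble each other more than those of pupils from different classes. A standard repeated-measures ANOVA or ANCOVA models correlation between occasions within a pupil, not correlation between pupils within a class. It therefore credits the face-to-face arm with more information than it has.

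The smaller arm is the clustered one, so it dominates the variance of the difference and the large online arm does little to dilute the error. These outcomes are the direct targets of the programme. A spurious difference between the two delivery formats, or an interval that looks more precise than it is, would bear on the claim that one format can replace the other.

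**Working it through.** The plan gives no sample size, power or precision for the secondary outcomes, so there is no stated figure to reproduce. The check asks how far the standard error of an online versus face-to-face mean difference is off if class is ignored.

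**Inputs from the protocol article (Sample size calculation):** 420 face-to-face and 2500 online pupils.

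**Assumptions, not in the document:** class size m = 25; ICC 0.02, 0.05 and 0.10 for the quantity analysed; clustering by class in the face-to-face arm only; equal outcome variance in both arms; planned numbers without loss; no further variance from the weights.

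**Step 1. Share of the variance.** Under independence, in units of the outcome variance: 1/420 + 1/2500 = 0.002381 + 0.000400 = 0.002781. The face-to-face arm contributes 0.002381/0.002781 = 86%.

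**Step 2. Design effect.** DE = 1 + (m − 1) × ICC, and effective face-to-face n = 420/DE.

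**Step 3. Standard error ratio.** R = √[(DE/420 + 1/2500) / (1/420 + 1/2500)].

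**Step 4. True error of a nominal 5% two-sided test.** 2 × [1 − Φ(1.96/R)]. Coverage of the nominal 95% interval is one minus this.

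| ICC | DE | Effective n | R | True type I error | True coverage |
|---|---|---|---|---|---|
| 0.02 | 1.48 | 284 | 1.19 | 9.9% | 90.1% |
| 0.05 | 2.20 | 191 | 1.42 | 16.9% | 83.1% |
| 0.10 | 3.40 | 124 | 1.75 | 26.2% | 73.8% |

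For example, at ICC 0.10: 3.40/420 + 0.000400 = 0.008495; 0.008495/0.002781 = 3.05; √3.05 = 1.75; 1.96/1.75 = 1.12.

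**Sensitivity to the assumptions.** Over class sizes of 20 to 30 and ICCs of 0.01 to 0.10, R runs from 1.08 to 1.87 and coverage from 93.1% to 70.6%. The direction is the same throughout; only the size changes.

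**Number of classes.** 420/25 = 16.8, about 17 classes. That is few enough for an uncorrected robust variance to be unreliable.

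**Link to the primary test.** The Study B Z-test also has no class term. At 15% transitions in both arms, a 5-point margin and 420/2500 pupils, power at one-sided 5% is 84.4% under independence. With m = 25 and a correct variance it is 72.3%, 58.7% and 45.0% at ICC 0.02, 0.05 and 0.10.

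**The case against.** The best case for the plan has four parts.

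- **Scope.** The Secondary outcomes section does not say that it covers Study B, whose stated objective is non-inferiority on new mental health problems. No secondary comparison is powered or declared confirmatory. This limits the weight of the point. It still applies to any online versus face-to-face comparison of these outcomes by the named method.
- **Place.** Leaving class out is not peculiar to ANOVA. The primary Z-test and the sample size do the same, and it matters more there. That is true, and both should be corrected together.
- **Size.** The factor rests wholly on an assumed class size and ICC. Adjusting for baseline may lower the ICC that counts. This also stands, which is why a range is shown.
- **Condensed article.** An article may leave modelling detail to the analysis plan. Here, however, it names a method, and that method as ordinarily run does not fit the stated design.

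Several stronger readings are tempting, but the text does not support them.

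- A reader might infer that pupils with a missed assessment are deleted, because complete-case analysis is the usual default of this method. Both study sections plan imputation under intention-to-treat, and neither limits it to the primary outcome.
- A reader might square the stated losses (0.85² = 0.72; 0.75² = 0.56) to get the share with both yearly follow-ups. But the 25% is given as "25% for the program-specific assessments of the online sample", not for the school-based follow-ups at 1 and 2 years, for which the online sample has no stated rate.
- A reader might charge the plan with the variance penalty of change scores against baseline adjustment, 2(1 − ρ)/(1 − ρ²), which is 1.33 at ρ = 0.5 and 1.18 at ρ = 0.7. Covariance analysis is already named, so this does not follow.
- A reader might expect a mixed model to recover lost data. Knowledge, self-esteem, stress symptoms and coping have one post-intervention assessment, so a baseline-adjusted mixed model gains almost nothing there.
- A reader might conclude that the non-randomised comparison goes unweighted. That is inferred only from the section not repeating the propensity weighting, and confounding would cause bias, not narrow intervals.
- A reader might carry the class-delivery argument over to Study A. Its pupils are randomised individually and use the programme on their own.

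**Conclusion.** The concern holds for online versus face-to-face comparisons of the continuous secondary outcomes, and only there. Run as named, the analysis treats classmates as independent and understates the standard error. With 420 and 2500 pupils, an assumed class size of 25 and an assumed ICC of 0.02 to 0.10, the factor is about 1.19 to 1.75 and a nominal 5% test errs about 10% to 26% of the time. The direction follows from the stated design; the size depends on two quantities the article does not give. No fault is established in the handling of missing data, in the use of baseline values or in Study A.

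**What to change.** For Study B secondary comparisons, replace the named method with a mixed model that has a random class effect in the face-to-face arm, or use class-robust variance with a small-sample correction. Adjust for the baseline value of the outcome where it is measured. State that the propensity weights and the imputation already planned in the Study B section also apply to these comparisons, and record class membership in the analysis data. Treat class in the same way in the primary Study B test, so that the two analyses agree.

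The cost is a few sentences of wording and slightly more programming, with no new outcome data. The downside is wider Study B intervals, because they would then reflect the information that the face-to-face arm carries.

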### Organization, quality assurance, and data management

Online questionnaires will be used for pseudonymized data collection. To ensure confidentiality, a unique identifying code not linked to the real name will be assigned to each participant. Data quality will be ensured by conducting automatic validity and range checks at data entry. All study-related data will be kept in a secure environment, stored for 10 years on protected servers at the principal investigator’s institution with regular back-up procedures in place. Data handling and access will follow German and European Union legal regulations concerning data protection and data security. The Coordination Center for Clinical Trials (KKS) Heidelberg will monitor study-related procedures at the five recruiting centers. Specifically, the recruitment of schools within the target regions and the recruitment of students within these schools will be monitored in order to ensure adherence to the study manual and documentation guidelines as well as equivalent procedures at all sites. Furthermore, an independent data and safety monitoring board (DSMB) will assess the progress of the trial, data safety, and the clinical efficacy endpoints.

### Safety reporting

There is no obvious risk for participating C&A. All participants will receive information on where to seek help for mental health problems within the ProHEAD Consortium.

### Dissemination

Results will be presented at national and international conferences and published in peer-reviewed international journals. The Internet-based approach guarantees that the intervention can be sustained at a relatively low cost, providing support for a large population—on condition that the intervention proves efficacious.

## Discussion

Schools as a setting of health promotion show various benefits [3, 4]. Accordingly, health-promoting activities following the life skills approach, including stress prevention and the promotion of mental health, are present at schools (see, e.g., [11, 12, 25, 26]). Empirical data show that school-based (predominantly face-to-face) interventions are promising [14, 24]. However, dissemination requires trained professionals. Internet-based delivery would allow the provision of health promotion to schools independent of their geographic location. Further benefits of Internet-based programs to promote mental health in C&A are evident: programs are easily accessible, attractive, and resource-saving. Nevertheless, until now, research on universal school-based online prevention programs has been largely lacking (for exceptions, see [19, 20, 30]). The present study aims to overcome the limitations of existing research by investigating the efficacy of an Internet-based health promotion program for C&A and its non-inferiority compared to the face-to-face setting. Key questions are the potentially positive and negative effects of the program *StresSOS*, focusing on stress management and mental health with regard to the two different formats, face-to-face and Internet-based. This also leads to questions about differential effects which will be investigated in this ProHEAD trial. For example, which of the invited participants will complete the online *StresSOS* program? Are there different program effects related to gender, age, or socioeconomic status? To our knowledge, this is the first adequately powered non-inferiority trial in the area of school-based mental health promotion and the first trial that systematically investigates help-seeking behavior as an outcome variable in a health promotion context. Cost-effectiveness studies are also rare in the context of universal school-based health promotion; the results of this trial will provide a basis for decision-makers in the field.

If online *StresSOS* proves efficacious and non-inferior to face-to-face delivery, it will have far-reaching implications for health promotion for C&A, both in and outside the school setting. Embedded in a nation-wide network of health professionals experienced in school-based prevention, *StresSOS* could be easily implemented into the routine, and thus would potentially have a significant impact on mental health promotion in C&A.

### Trial status

Recruitment of the participants has not yet begun. The recruitment period for the trial will start in October 2018 with the school-based baseline assessment within the ProHEAD Consortium and last until March 2020.

## Abbreviations

AHSQ: Actual Help-Seeking Questionnaire
AUDIT: Alcohol Use Disorders Identification Test
BASH-B: Barriers to Adolescents Seeking Help Scale
C&A: Children and adolescents
CEAC: Cost-effectiveness acceptability curve
CRAFFT-d: Car, Relax, Alone, Forget, Friends, Trouble
DRKS: German Clinical Trials Register
DSMB: Data and safety monitoring board
DSM-IV: Diagnostic and Statistical Manual of Mental Disorders, fourth edition
GHSQ: General Help-Seeking Questionnaire
IASMHS: Inventory of Attitudes Toward Seeking Mental Health Services
ICER: Incremental cost-effectiveness ratio
ITT: Intention-to-treat
KIDSCREEN-10: Health-related quality of life measure for C&A
KKS: Coordination Center for Clinical Trials
MHL: Mental health literacy
MRV: Mannheimer Modul zum Ressourcenverbrauch
PHQ-A: Patient Health Questionnaire-9 modified for Adolescents
ProHEAD: Promoting Help-seeking using E-technology for ADolescents
QALY: Quality-adjusted life year
RCT: Randomized controlled trial
SAPAS: Standardized Assessment of Personality – Abbreviated Scale
SDQ: Strengths and Difficulties Questionnaire
SEED: Short Evaluation of Eating Disorders
SEKJ: Inventory of Self-Esteem for Children and Adolescents
SSKJ 3–8 R: Stress and Coping Questionnaire for Children and Adolescents
WCS: Weight Concerns Scale
WTP: Willingness-to-pay
